## **5 ENDPOINTS**

### **5.1 Primary Endpoint**

The following primary endpoint will be examined:

Adjudicated Composite rate of all Death, all Myocardial Infarction (MI) and Target Vessel Revascularization (TVR) at 1 year.

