#### **6.5 Patient Discontinuation**

Patients are considered enrolled in the study from the time of Registration or Randomization. Every patient should remain in the clinical evaluation until completion of the required follow-up period, however, a patient's participation in any clinical evaluation is voluntary and the patient has the right to withdraw at any time without penalty or loss of benefit. Should this occur, the reason for withdrawal must be documented in the source documentation. Conceivable reasons for discontinuation may include, but not be limited to, the following:

**Patient Withdrawal:** Patient participation in a clinical investigation is voluntary and the patient may discontinue participation (refuse all subsequent testing/follow-up) at any time without loss of benefits or penalty.

**Investigator Termination:** Investigator may terminate the patient's participation without regard to the patient's consent if the Investigator believes it is medically necessary.

**Lost-to-Follow-up:** Patient does not complete the scheduled follow-up visits but has not 'officially' withdrawn from the clinical evaluation. (Does not apply to missed visits). Site personnel should make all reasonable efforts to locate and communicate with the patient, including the following, at each contact time point:

- A minimum of two telephone calls to contact the patient should be recorded in the source documentation, including date, time, and initials of site personnel trying to make contact.
- If these attempts are unsuccessful, a certified letter should be sent to the patient and/or the patient's General Practitioner/Family Doctor. (this should be done only when the patient has consented to direct contact with General Practitioner/Family Doctor)
- If a patient misses one or more of the follow-up contact time points it will be considered a missed visit. Patient may then return for subsequent visits. If the patient misses two

consecutive time points and the above-mentioned attempts at communicating with the patient are unsuccessful, the patient will be considered lost-to-follow-up.

A Study Completion form must be completed when,

- the patient is considered lost to follow-up per the above definition or
- the patient withdraws from the Clinical Evaluation or
- the investigator withdraws the patient from the Clinical Evaluation or
- the patient has died or
- upon Clinical Evaluation completion (5 year follow-up time point has been reached)

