### ***9.6 Procedures for Accounting for Missing Data***

Analyses will be based on available data, missing data excluded. Any unused or spurious data will be noted as appropriate in the final report.

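### Section 6.5 allows a patient to be closed as lost to follow-up before the 1-year primary endpoint is due, and nothing then requires an attempt to establish her 1-year status

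*Protocol*

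**What the plan says.** The Protocol's primary endpoint (section 5.1) is the "Adjudicated Composite rate of all Death, all Myocardial Infarction (MI) and Target Vessel Revascularization (TVR) at 1 year". Section 8.1 sets clinical contacts for all patients at 30 ± 7 days, 240 ± 14 days, 1 year ± 28 days and then yearly to 5 years, each by telephone or office visit.

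Section 6.5 lists loss to follow-up among the reasons for discontinuation. At each time point, "A minimum of two telephone calls to contact the patient should be recorded in the source documentation". It continues: "If these attempts are unsuccessful, a certified letter should be sent to the patient and/or the patient's General Practitioner/Family Doctor", with the doctor contacted only if the patient has agreed. Missing a time point is not in itself loss to follow-up: "Patient may then return for subsequent visits". Two conditions together make it so. When a patient misses two "consecutive time points and the above-mentioned attempts at communicating with the patient are unsuccessful, the patient will be considered lost-to-follow-up".

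The administrative consequence follows in the same section. "A Study Completion form must be completed when" any of five situations arises. One is that "the patient is considered lost to follow-up per the above definition or"; the others are withdrawal by the patient, withdrawal by the investigator, death, and reaching 5 years. The sponsor and the ethics committee are then informed.

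For the analysis, section 9.6 states: "Analyses will be based on available data, missing data excluded". Section 9.4 reports the primary endpoint as counts, percentages and exact 95% confidence intervals.

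**The concern.** The first two scheduled contacts both come before the primary-endpoint time point, so the two-miss rule can be met before that endpoint is due. Contact attempts are tied to each contact time point, and once a patient has been declared lost no section expressly requires a further attempt at 1 year. The same gap exists later: a patient missed at years 1 and 2 can be closed with the contacts at years 3, 4 and 5 still to come.

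Death, MI and revascularization are dated events. They can often be established afterwards through a later call, the family doctor or a hospital record, so an unanswered day-240 contact need not mean that 1-year status can never be known. Patients who cannot be reached may also differ in outcome from those who can, for example because they died or were treated elsewhere. If so, the missingness is related to the outcome, and an analysis restricted to available data would tend to understate the composite rate without the confidence interval showing it.

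**Working it through.** **Inputs.** Contact windows: section 8.1. Loss-to-follow-up conditions: section 6.5. Single Arm Study size of 1550, expected 1-year drop-out of 3%, assumed true rates of 10% to 14% and half-width of 1.5% to 1.7%: section 9.2. One year is taken as 365 days. The 12% rate used below is the midpoint of the plan's range. The 2- to 3-fold event rate in missing patients is my assumption; the Protocol gives no figure for it.

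**1. The plan's own precision.** Half-width = 1.96 × √(p(1 − p)/n).
- n = 1550, p = 0.10: 1.49%.
- n = 1550, p = 0.14: 1.73%.

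This reproduces the stated 1.5% to 1.7%. The exact Clopper-Pearson half-widths are slightly larger, at 1.53% and 1.76%.

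**2. When the rule can be met.**
- 30-day window: 30 ± 7 = days 23 to 37.
- 240-day window: 240 ± 14 = days 226 to 254.
- 1-year window: 365 ± 28 = days 337 to 393.

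If the first two contacts are missed, the visit condition is met when the 240-day window closes, on day 254. That is 337 − 254 = 83 days before the 1-year window opens and 365 − 254 = 111 days before the nominal anniversary. Among the contacts in section 8.1, this is the only pair that can close a patient before 1 year. The next pair, 240 days and 1 year, ends with the 1-year window itself on day 393.

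**3. What the site must have tried by then.** At least two calls at each of two time points (2 × 2 = 4 calls) and a letter at each (2 letters), all without success.

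**4. Loss of precision.** If the whole 3% were missing, n = 1550 × 0.97 ≈ 1504, a loss of about 46 patients. The half-width becomes 1.52% at p = 0.10 and 1.75% at p = 0.14. The widening is only 0.02 to 0.03 percentage points, so precision is not the issue.

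**5. Ceiling on bias.** Bias = missing fraction × (rate in the missing − rate in the observed).
- Missing patients at twice 12%: 0.03 × (24% − 12%) = 0.36 points.
- Missing patients at three times 12%: 0.03 × (36% − 12%) = 0.72 points.

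**6. Extreme bounds at 3% missing.** The lower bound assumes no events among the missing, 0.97p; the upper assumes all had events, 0.97p + 0.03.
- Observed 10%: true rate between 9.7% and 12.7%.
- Observed 14%: true rate between 13.6% and 16.6%.

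Steps 4 to 6 charge the entire expected drop-out to this rule. The share that it actually causes is not given and lies anywhere between none and all of it.

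**The case against.** The strongest case on the other side is that section 6.5 is an ordinary retention rule and that little follows from it. Much of that case stands.

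- **Two misses alone do not close a patient.** The required calls and letters must also have failed, and the definition expressly leaves out missed visits. This stands. The protection is partial, though: a contact may itself be a telephone call, so a missed contact may already be a failed attempt, and the letter may go to the patient without any approach to her doctor.
- **No data are discarded.** A reader might infer that recoverable primary-endpoint data are thrown away by rule. The Protocol does not say so. Events already recorded remain available data, nothing says that the Study Completion form locks the record, and nothing bars information that surfaces later. Section 8.1.1 also asks for all efforts to obtain information on patients seen or treated at non-study hospitals. That duty does not, however, extend to a search for a patient already declared lost.
- **No contradiction.** A reader might see a conflict between the sentence allowing a patient to return and the one declaring her lost. They fit together: the first covers missed visits, the second covers patients who also cannot be reached.
- **No shown difference between cohorts.** A reader might infer a stricter rule in the randomized sub-study because of its 270-day visit. Section 8.1 does not list that visit among the contacts for all patients, and section 8.2 presents the angiography as additional to them. The Protocol does not say that it counts toward the two misses.
- **Little rides on it.** The primary endpoint is descriptive, and success of the sub-study rests on in-stent late loss. How a partly followed patient enters the 1-year denominator may properly be left to the statistical analysis plan.

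What remains is that no 1-year status check is required for a patient declared lost before 1 year.

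**Conclusion.** The point holds in a limited form. Section 6.5 permits follow-up to end by day 254, 83 days before the 1-year window opens, with no duty afterwards to establish death, MI or target vessel revascularization at 1 year. Section 9.6 then excludes what is missing.

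The effect of the rule itself cannot be calculated from the Protocol. It is confined to patients who were unreachable at both early contacts and whose status a later attempt would have recovered; that number may be close to zero. The range of 0.36 to 0.72 points is a ceiling resting on two assumptions: that all of the 3% drop-out arises through this rule, and that these patients have 2 to 3 times a 12% event rate. Even then it is less than half of the planned half-width (0.72/1.5 = 0.48). This is an inexpensive improvement to a rule that touches the primary endpoint. It does not undermine the design.

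**What to change.** Amend the loss-to-follow-up paragraph of section 6.5 to state three things.

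1. Classing a patient as lost to follow-up does not end contact attempts.
2. The same calls and letter, with family-doctor contact or a record check where the patient has consented, are repeated at later time points, and at minimum at 1 year, before her follow-up is closed.
3. Dated information on death, MI and revascularization obtained later counts toward the time point at which the event occurred.

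There is no need to hold every unreachable patient open until the 5-year window closes; the gap shown here is met by the three statements above. The cost is an amendment to one paragraph and repeat calls, letters or record checks for a small number of patients. The expected drop-out of about 46 of 1550 at 1 year is an upper guide to that number in the Single Arm Study. No extra patients or study procedures are needed.

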## **7 TREATMENT OF PATIENTS**

The schedule of events for this clinical evaluation is located in Appendix V.

### ***7.1 Pre-Procedure (Baseline)***

#### **7.1.1 Patient History**

Patient history will include demographics (e.g., age), symptoms at presentation and referral path, cardiac history including but not limited to Canadian Cardiovascular Society (CCS) and Braunwald classification of angina, history of myocardial infarction, diabetes mellitus, renal insufficiency, left ventricular dysfunction, hypertension, hypercholesterolemia, previous CABG and PCI. Data recorded will also include menopausal, status/years since onset of menopause, hysterectomy status, oophorectomy status, use of weak estrogens (black cohosh, soy, red clover), past and present use of hormonal contraceptives/hormone replacement therapy (including mode of administration), smoking history, educational/professional/social status such as number of children, cohabitation, employment and educational degree, body surface area and chronic concomitant medications (Refer to Appendix II for Definition).

#### **7.1.2 Laboratory Assessments**

Routine hospital blood-work should be taken for all patients per hospital standards for patient management. Additional samples for local (all patients) and central laboratory measurements (for patients enrolled in the randomized sub-study) must be taken as described below.

The following laboratory assessments must be obtained within 7 days prior to the index procedure:

| Local laboratory for all patients                                 | Central laboratory for patients enrolled in randomized sub-study |
|-------------------------------------------------------------------|------------------------------------------------------------------|
| Creatine kinase myocardial-band isoenzyme (CK-MB) or Troponin I/T | Creatine kinase myocardial-band isoenzyme (CK-MB)                |
| Pregnancy test (if applicable)                                    | Total Cholesterol, HDL, LDL, triglycerides                       |
|                                                                   | High-sensitivity C-reactive protein (hs-CRP)                     |
|                                                                   | Glycosylated hemoglobin (HbA 1c )                     |
|                                                                   | 17 $\beta$ -estradiol                                            |
|                                                                   | Estrone                                                          |
|                                                                   | FSH level                                                        |
|                                                                   | Free Testosterone                                                |
|                                                                   | Dehydroepiandrosterone (DHEA)                                    |
|                                                                   | Androstenedione                                                  |
|                                                                   | Sex Hormone Binding Globulin (SHBG)                              |
|                                                                   | Homocysteine                                                     |
|                                                                   | Creatinine                                                       |

### 7.1.3 Other Assessments

The following parameters must be measured within 7 days prior to the index procedure:

- ECG
- Height (cm)
- Weight (kg)
- Waist circumference at umbilical level (cm)
- Blood pressure

### 7.1.4 Medications

Patients selected for coronary stenting should receive a loading dose of antiplatelet medications (unless patient is under chronic antiplatelet medications) prior to the start of the procedure, but no later than one hour post procedure. Medications administered will include loading dose of clopidogrel bisulfate ( $\geq 300$  mg) and aspirin ( $\geq 75$  mg). Ticlopidine at a dose standard with hospital practice may be substituted for clopidogrel, as required by hospital practice or if the patient develops hypersensitivity to clopidogrel. If patient is already receiving clopidogrel bisulfate (or ticlopidine hydrochloride), loading dose can be adjusted per physician's discretion, but not omitted.

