## **4.2 Treatment Strategy**

### **The treatment strategy for all patients enrolled in the clinical evaluation is as follows:**

The treatment strategy will be determined by the Investigator. It is recommended that each enrolling investigator review the most recent IFU to assess contraindications, warnings, and precautions for treating potential patients.

Loading dose of clopidogrel of at least 300 mg prior to the start of the procedure. This dose may be adjusted if the patient is already taking clopidogrel. Recommended prior to the start of the procedure, however no later than 1 hour post procedure.

No non-study percutaneous procedures can be performed at the time of the study procedure

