#### **11.2.2 Clinical Investigation Plan Deviations**

It is the investigator's responsibility to ensure that there are no deviations from the clinical investigation plan without notification and approval of Sponsor and full compliance with all established procedures of the MEC. The investigator will not deviate from the clinical investigation plan for any reason without prior written approval from Sponsor, except in cases of medical emergencies, when the deviation is necessary to eliminate an apparent immediate hazard to the patient. In that event, the investigator will notify Sponsor and document the deviation in the electronic CRF. The investigator will inform the MEC of all clinical investigation plan deviations according to each hospital's MEC requirements. In the event of any deviation from the clinical investigation plan, a clinical investigation plan deviation eCRF will be completed. The occurrence of clinical investigation plan deviations will be monitored by Sponsor for evaluation of investigator compliance to the clinical investigation plan and regulatory requirements.

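### Section 7.1.4 waives the antiplatelet loading dose for patients on chronic antiplatelet drugs, but its own last sentence forbids omission and section 4.2 gives no waiver

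*Protocol*

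**What the plan says.** Two sections of the protocol govern the antiplatelet load.

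Section 7.1.4 (Medications, under the pre-procedure heading) opens by saying that patients selected for stenting "should receive a loading dose of antiplatelet medications (unless patient is under chronic antiplatelet medications) prior to the start of the procedure", with one hour after the procedure as the outer limit. Its second sentence gives the content without any exception: "Medications administered will include loading dose of clopidogrel bisulfate" (at least 300 mg) and aspirin (at least 75 mg). The third lets ticlopidine replace clopidogrel. The fourth and last deals with patients already on clopidogrel or ticlopidine: for them the "loading dose can be adjusted per physician's discretion, but not omitted".

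Section 4.2 introduces its list with "The treatment strategy for all patients enrolled in the clinical evaluation is as follows". The list includes "Loading dose of clopidogrel of at least 300 mg prior to the start of the procedure" and one relaxation: "This dose may be adjusted if the patient is already taking clopidogrel".

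Section 11.2.2 sets the consequence of departing from these rules: "In the event of any deviation from the clinical investigation plan, a clinical investigation plan deviation eCRF will be completed".

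**The concern.** A patient on long-term clopidogrel or ticlopidine falls under both the first and the last sentence of 7.1.4. The first says she need not be loaded; the last says the load must not be left out. A site cannot follow both.

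The parenthesis also reaches further than its author probably meant. It refers to antiplatelet medication in general, so it covers a patient taking only aspirin. Taken literally, she is excused from the clopidogrel load although she has no clopidogrel or ticlopidine on board. Section 4.2 requires the load in her case and does not even permit adjustment.

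At stake are a usable instruction on antiplatelet cover around stent implantation and consistent recording of deviations across up to 130 sites. Nothing in the statistical design depends on it.

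**Working it through.** No arithmetic applies: the point rests on no sample size, power, error rate or event count. The check is to take each type of patient and read off what each statement requires.

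| Patient at the time of the procedure | 7.1.4, parenthesis in first sentence | 7.1.4, last sentence | 4.2 |
|---|---|---|---|
| On chronic clopidogrel | Load waived | Load adjustable, must not be left out | Load required, adjustable |
| On chronic ticlopidine | Load waived | Load adjustable, must not be left out | Load required; ticlopidine users not mentioned |
| On chronic aspirin only | Load waived | Does not apply | Clopidogrel load of at least 300 mg required, no adjustment offered |
| On no chronic antiplatelet drug | No waiver | Does not apply | Clopidogrel load of at least 300 mg required |

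1. **Clopidogrel or ticlopidine users.** The parenthesis and the last sentence of 7.1.4 contradict each other directly. Section 4.2 also conflicts with the waiver: permission to adjust a required dose is not permission to leave it out.
2. **Aspirin-only users.** The last sentence of 7.1.4 does not reach them, so nothing in that sentence overrides the waiver. The conflict is with 4.2, and also with the second sentence of 7.1.4, which lists clopidogrel among the drugs given without exception.
3. **Patients on no antiplatelet drug.** There is no conflict.

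Of the three statements that bear on pretreated patients, the parenthesis is the one that does not fit.

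**Deviation status of an omitted clopidogrel load:**

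- Clopidogrel or ticlopidine user: compliant under the parenthesis, a deviation under the last sentence of 7.1.4.
- Aspirin-only user: compliant under the parenthesis, a deviation under 4.2.

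Section 11.2.2 requires a deviation form for any departure, so identical conduct can be recorded at one site and not at another.

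**The case against.** Several points can be made for leaving the text alone.

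- **The specific sentence governs the general one.** On that reading the last sentence of 7.1.4 overrides the parenthesis for clopidogrel and ticlopidine users. This is reasonable and may be how sites act. The protocol states no such precedence, however, and the reading does nothing for aspirin-only users.
- **The parenthesis was meant for aspirin.** The aspirin load of at least 75 mg equals the daily maintenance dose, so a patient already on aspirin needs no separate load. This is a plausible intention, but the text does not say it.
- **No site would drop the clopidogrel load for an aspirin user.** The second sentence of 7.1.4 and section 4.2 both point the other way. That makes the error less likely in practice; it also confirms that the parenthesis is the statement out of line.
- **The parenthesis relaxes only the timing.** The exception is attached to receiving the load and comes before the timing phrase, so the grammar does not support this.
- **Section 4.2 does not itself forbid omission and does not name ticlopidine.** This is correct. Section 4.2 conflicts with the waiver because it requires the load and allows only adjustment. Its wording is less complete than the last sentence of 7.1.4, which is why the fix touches it too.
- **The consequence is small.** This stands. Adjustment is left to the physician with no minimum dose, so for clopidogrel and ticlopidine users the gap between a much reduced load and none is narrow. The instruction is phrased as what patients should receive, and 4.2 leaves treatment strategy to the investigator.

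**Conclusion.** The concern holds as a minor internal contradiction in an operative dosing rule. The parenthesis in 7.1.4 conflicts with the last sentence of its own paragraph for clopidogrel and ticlopidine users, and with 4.2 for them and for aspirin-only users.

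The number of patients affected cannot be derived, because the protocol does not give the proportion on chronic antiplatelet drugs. The conclusion rests on the literal wording and on the absence of any stated order of precedence between the sentences. It claims no effect on event rates, power, error rate or the comparison between arms. The gain is one clear rule on antiplatelet cover and one way of coding deviations.

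**What to change.** In 7.1.4, delete the parenthesis, or limit it to the aspirin load. That alone removes the contradiction.

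In 4.2, bring the relaxation into line with the last sentence of 7.1.4, for example: *This dose may be adjusted, but not omitted, if the patient is already taking clopidogrel or ticlopidine.* The existing provision for ticlopidine at the hospital's usual dose can stay as it is.

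The single rule is then that every patient receives a clopidogrel load, or ticlopidine where it is substituted. It may be adjusted but not left out in those already taking either drug, and any omission goes on the deviation form that 11.2.2 already requires.

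The cost is one parenthesis removed or narrowed and a few words added. No design element, sample size or analysis changes.
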